### Baseline Measures

After pre-participation screening is completed and informed consent is obtained, baseline measures will be collected on the same day.

#### Numeric Pain Rating Scale (NPRS) and Pain Diagram

The 11-point NPRS will be used to structure 3 measurements of subjects' pain intensity, including the levels at best in the past 24 hours, at worst in the past 24 hours, and the current level of pain. The NPRS ranges from "No Pain" and "Worst Imaginable Pain." NPRS measurements are reliable and valid for use in clinical trials [48]. A pain diagram will be used to record the location and nature of a patient's ankle and foot symptoms by drawing it on the diagram of a human figure.

#### Fear Avoidance Beliefs Questionnaire (FABQ)

The FABQ is a questionnaire intended to quantify the level of fear of pain during various activities in individuals with lower back pain [49]. It consists of a Physical Activity subscale (4 items) and Work subscale (7 items) and 5 distractor items. The subscales of the FABQ demonstrate high test-retest reliability (ICC_2,1_=.77 and .90, respectively) [50]. Each subscale has been demonstrated to be significantly predictive of current and future disability in individuals with acute and chronic lower back pain [49,51,52]. Wording will be changed to reference lower extremity disability for purposes of this study. Preliminary data regarding clinimetric properties of the modified FABQ will be collected during this study in order to conduct future validation analyses.

#### Lower Extremity Self Efficacy Scale (LExSES)

The LExSES is a 20-item questionnaire intended to measure a subjects' self-efficacy related to lower extremity function. It consists of 3 subscales of patient self-efficacy, including functional and self-regulatory abilities, and exercise performance self-efficacy. Preliminary data regarding clinimetric properties of the LExSES also will be collected during this study in order to conduct future validation analyses.

#### Positive and Negative Affect Scale (PANAS)

The PANAS is an inventory aimed at assessing a patients' mood. It consists of two checklists, each containing 10 items [53]. Patients are requested to rate each item to describe their mood in the timeframe provided using a 5-point Likert scale. The response scale ranges from 1 "Very slightly or not at all" to 5 "Extremely." The PANAS shows high internal consistency, test-retest reliability, and sensitivity to change.

#### Patient Global Rating of Change (GROC)

The GROC is a single item 15-point scale intended to measure a subject's general perception regarding response to treatment [54]. Responses range from "A very great deal better" to "A very great deal worse," with "About the same" serving as the center of the scale. GROC is a common scale used in studies that assess health-related quality of life due to its simplicity and face validity.

#### Lower extremity ROM

Hip flexion with knee flexed, internal rotation, external rotation; knee extension; subtalar inversion and eversion; and ankle plantarflexion and dorsiflexion passive ROM will be measured with a standard goniometer by the evaluating therapist using previously described techniques that demonstrate adequate validity and reliability [55-58]. An inclinometer will be used to measure hip extension range of motion in a Thomas test position with both the knee flexed and extended [59,60] and the inclinometer placed just proximal to the patella and parallel with the long axis of the thigh.

#### Lower extremity manual muscle testing (MMT)

MMT of the gluteus medius, gluteus maximus, quadriceps, tibialis posterior, tibialis anterior, peroneus longus/brevis (group), and gastocnemius will be completed according to established procedures and grading scheme [59]. Pain and inability to maintain the test position at a given level of resistance will be included as criteria to discontinue the tests. These tests retain adequate validity and intra-rater reliability to detect muscle weakness, although they may demonstrate ceiling effects that depend on examiner characteristics [61].

#### Star balance excursion test (SBET)

The SBET is a clinical test of dynamic balance [62-65]. Subjects will assume unilateral stance in the center of a grid marked circumferentially in 45-degree increments. After a learning trial consisting of 6 repetitions in each of the 8 test directions [63], subjects will complete 3 repetitions of single limb squat reach. Two trials will be completed: 1 trial each with the subject standing on the affected and unaffected limbs. Test directions include anterior, lateral, anterolateral, posterolateral, posterior, medial, anteromedial, and posteromedial. The evaluating therapist will record the distance achieved between the stance toe and heel of the reaching extremity for 3 repetitions in each direction. Fifteen seconds of rest will be provided between trials. Repetitions will be excluded if the subject (1) is unable to maintain weightbearing during the trial; (2) lifts the stance foot; (3) loses balance; or (4) does not maintain the hold or start positions for 1 second. This test demonstrates good reliability (ICC_2,1 _= .67-.97), and demonstrates discriminative validity between non-disabled individuals and patients with chronic ankle instability [64,66].

### Randomization and blinding

After completing pre-participation screening and baseline measures by a standardized licensed physical therapist (evaluating therapist), each subject will receive both an identification number and a unique random number indicating treatment group assignment. Numbers indicating group assignments will be concealed in a privacy envelope. A second licensed physical therapist blinded to the baseline examination (treating therapist) will open the proper randomization envelope that corresponds to the patient's unique identification number. The treating therapist will record the subject's group assignment on a standardized form. It will be impossible to blind the subject and treating therapist to treatment assignment. However, the evaluating therapist will remain blind to the subject's treatment assignment. Patients will be instructed to conceal their group assignment from the evaluating therapist.

### Experimental groups

Subjects will be randomized into 3 groups after pre-participation screening is completed, informed consent is obtained, and baseline measures are recorded (Figure 2). The first group (n = 63) will receive talocrural traction manipulation (Figure 3). With the subject in a seated position on a treatment table and the lower extremity of interest stabilized to the table with a belt, the standardized treating therapist will grasp the foot of interest with the thenar eminences on the foot's plantar surface. A thrust will be delivered parallel to the long axis of the subject's lower leg after the treating therapist induces passive ankle dorsiflexion to end range. The second group (n = 63) will receive talocrural traction mobilization. Traction will be delivered to the talocrural joint at the treating therapist's second perception of tissue resistance in 3 bouts of 30-second holds, separated by 10 seconds of rest. The third group (n = 63) will receive the manual therapy control intervention. This will consist of the same patient and clinician preparation for the mobilization/manipulation techniques. However, the treating therapist will maintain passive DF ROM for the duration of 1 deep inhalation and exhalation by the subject. Following the procedure, all subjects will receive range of motion exercises involving 10 clockwise ankle and foot circles within a symptom-free range of motion. Subjects will be requested to complete this exercise 4 times daily for 10 repetitions each session.

**Figure 2 F2:**
[figure not shown]
**Flow chart for subject screening, pre-intervention measurement, intervention, and post-intervention measurements**.

**Figure 3 F3:**
[figure not shown]
**Ankle high-velocity low-amplitude, slow velocity, and control interventions under study**. With the subject in a supine position on a treatment table and the lower extremity of interest stabilized to the table with a belt (A), the treating investigator will grasp the foot of interested with the thenar eminences on the foot's plantar surface (B) and induce passive dorsiflexion to end range (B; open arrow). Iatrogenic force will be provided along the long axis of the tibia in the intervention groups. (B; hatched line) In the control group, the treating investigator will maintain passive dorsiflexion (B; open arrow) for the duration of 1 deep inhalation and exhalation by the subject rather than induce an iatrogenic force.

### Treatment schedule

All subjects will attend 5 treatment sessions as part of this study, including 2 sessions during the first week and 1 session per week for the next 3 consecutive weeks. All subjects will be scheduled for the first treatment session within 3 days of the baseline examination. In all treatment groups, the first 2 sessions will begin with delivery of the ankle manual therapy technique followed by the range of motion exercise described above. The final 3 sessions will involve instruction in a standardized strengthening program. The treating therapist will document daily treatment on a standardized form, as well as their subjective impression of the subject's improvement at 4 weeks after enrolment. Subjects will be requested to document home program compliance on a standardized log, and advised to refrain from new activities during the study. Clinicians and subjects will be free to pursue their treatments of choice after the 4-week measurements are obtained.

### Post-treatment measures and schedule

The FAAM, NPRS, FABQ, PANAS, LExSES, and a side effect questionnaire will be administered at 1 week following enrolment. The demographic questionnaire, FAAM, NPRS, FABQ, PANAS, and LExSES will be administered at 4 weeks following enrolment, and mailed to subjects to complete at 6 months, 1 year, and 2 years following enrolment.

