### Data Analysis

The primary dependent variable for this study is FAAM score at 1 week, 4 weeks, 6 months, 1 year, and 2 years. Secondary dependent variables include NPRS, modified FABQ, PANAS, LExSES, and GROC scores at 1 week, 4 weeks, 6 months, 1 year, and 2 years. The independent variable is the manual therapy intervention condition. All other outcome measures will be assessed as potential covariates of treatment success, which is defined as the achievement of minimum clinically important change score on the FAAM for this study.

Descriptive statistics will be calculated for the data set, including frequencies, means, and standard deviations. Between and within-group comparisons will be made for outcome measurements at 4 weeks, 6 months, 1 year, and 2 years post-enrolment. Analysis of variance with appropriate post-hoc pairwise comparisons will be used to assess between-groups differences for continuous data. Statistical significance of between-group differences in categorical data will be assessed with chi square analysis. Pearson correlations and multivariate linear regression analyses will be performed to determine statistical significance of associations with treatment success and failure. An intention-to-treat analysis will be performed for subjects who drop out of the study after enrolment but prior to completion of all study procedures. Statistical significance of inferential statistical tests will be accepted at α≤.05.

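### The only scheduled side effect questionnaire is at 1 week, so delayed reactions and reactions when strengthening starts are not systematically asked about

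*Protocol article*

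**What the plan says.** The Protocol article, Post-treatment measures and schedule, gives two explicit lists of instruments. The 1-week list has five self-report scales (FAAM, NPRS, FABQ, PANAS, LExSES) and one harm instrument: "a side effect questionnaire will be administered at 1 week following enrolment". The second list reads "The demographic questionnaire, FAAM, NPRS, FABQ, PANAS, and LExSES will be administered at 4 weeks following enrolment", and the same set is then "mailed to subjects to complete at 6 months, 1 year, and 2 years following enrolment". The side effect form is not in it.

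Treatment schedule plans five sessions, "including 2 sessions during the first week and 1 session per week for the next 3 consecutive weeks". In every group "the first 2 sessions will begin with delivery of the ankle manual therapy technique followed by the range of motion exercise", and after that "The final 3 sessions will involve instruction in a standardized strengthening program". On the start of treatment: "All subjects will be scheduled for the first treatment session within 3 days of the baseline examination".

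Data Analysis names the FAAM as primary dependent variable and NPRS, modified FABQ, PANAS, LExSES and GROC as secondary ones. Side effects are not named. On comparison times it says: "Between and within-group comparisons will be made for outcome measurements at 4 weeks, 6 months, 1 year, and 2 years post-enrolment".

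**The concern.** The article fixes when side effects are asked about, so this is not a detail left to a fuller document. The questionnaire is tied to enrolment, while the technique is tied to treatment sessions that may start some days later. A reaction to the second technique session may have had little time to appear when the form is filled in, or the session may not yet have taken place. After that no scheduled instrument asks about side effects, although strengthening starts in this period on ankles that received a thrust, a slow traction or a placebo hold.

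At stake is whether the trial can describe how well the three conditions were tolerated over the 4-week treatment period. Benefit is followed to 2 years. Side effects are asked about once, and the analysis section names no outcome for them.

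**Working it through.** **Inputs (all Protocol article)**
- Side effect questionnaire: day 7 after enrolment (Post-treatment measures and schedule).
- Sessions: 2 in the first week, then 1 a week for 3 weeks; technique in the first 2 only (Treatment schedule).
- Day of the first session: s = 0 to 3 after the baseline examination (Treatment schedule). I take enrolment and baseline as the same day, because Baseline Measures puts the baseline assessment on the day of screening and consent.
- Home ankle exercise: 4 times a day, no duration given (Experimental groups). **Assumption:** it ends at the 4-week measurements, day 28.

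**1. Session count.** 2 + 3 × 1 = 5, which reproduces the plan's figure. Sessions after the first week: 5 − 2 = 3. All 3 are strengthening instruction, with no difference between groups described.

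**2. Timing of the second technique session.** The article does not say where the first week starts.
- Counted from enrolment, the week ends on day 7. Both technique sessions come no later than the questionnaire, but the second can fall on day 7 itself.
- Counted from the first session, the week ends on day s + 7, that is day 7, 8, 9 or 10 for s = 0, 1, 2, 3. The second session can then fall up to 3 days after the questionnaire.

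**3. Home exercise after the questionnaire.** Share = 1 − (7 − s)/(28 − s).

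| s | Days covered | Programme days | Share after the questionnaire |
|---|---|---|---|
| 0 | 7 | 28 | 75.0% |
| 1 | 6 | 27 | 77.8% |
| 2 | 5 | 26 | 80.8% |
| 3 | 4 | 25 | 84.0% |

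**4. What else could pick up a later reaction?**
- NPRS asks about current pain and the best and worst of the last 24 hours (Numeric Pain Rating Scale and Pain Diagram). A flare in week 2 or 3 that settles before the 4-week visit leaves no trace.
- FAAM scores function. It does not record events or their cause.
- GROC is an outcome in Data Analysis but is in neither list under Post-treatment measures and schedule.
- The treating therapist completes a standardized form on daily treatment. Whether it asks about harms is not described, and this therapist knows the assignment (Randomization and blinding).

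**The case against.** The strongest defence is that the questionnaire sits where it matters. The randomized contrast is the manual technique, which is given only in the first two sessions, both in the first week. The later sessions and the home exercise are the same in all arms, and the exercise is ankle circles kept inside the symptom-free range. Asking about side effects soon after the technique is a reasonable choice. Most of this stands. The 3-of-5 count and the 75% to 84% share describe exposure common to all arms and say little about differences between them. Two things remain: the second technique session may fall on or after the day of the questionnaire, and the same strengthening programme may be tolerated differently after different techniques.

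A reader might infer that harms from the last 3 sessions, or late effects of the thrust, are never collected. The documents do not support that. The treatment form's content is not shown, spontaneous reporting is commonly left to the full protocol, and lasting pain or loss of function would partly show in NPRS and FAAM to 2 years.

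A reader might also infer that side effects will go uncompared because 1 week is missing from the comparison times. That does not follow either. The same section names 1 week for the primary and secondary variables, so the omission is an inconsistency touching every 1-week outcome. Chi-square tests are planned for categorical data in general.

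**Conclusion.** The point holds in a limited form. The stated schedule contains one structured side effect enquiry, at 1 week after enrolment, and leaves it out of the 4-week set. Depending on how the first week is counted, the second technique session can fall as late as the day of that enquiry or up to 3 days after it. Delayed reactions, and reactions when strengthening starts, are not systematically asked about. The scheduled scales are weak substitutes for a transient event.

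The timing result assumes that enrolment and baseline are the same day. The home-exercise share also assumes a programme ending at 4 weeks, which the article does not state; without that assumption no share can be given. The conclusion concerns how completely side effects are ascertained. It does not show that harms go unrecorded altogether, and it does not affect sample size or the significance level.

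**What to change.** 1. In Post-treatment measures and schedule, add the same side effect questionnaire to the 4-week set, asking about the time since the last questionnaire. This brings the second technique session, whenever in the first week it falls, and the strengthening phase up to that contact under structured questioning.
2. In Data Analysis, name the proportion of subjects with any side effect by 4 weeks (reported on either form) as an outcome, compared across the three groups with the chi-square test already planned for categorical data.
3. State whether the first week is counted from enrolment or from the first session, so that the order of questionnaire and second session is clear.

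The cost is one existing form at an existing contact, one table, and a few more minutes of questionnaire time per subject. It is best done before subjects pass their 4-week visit, because afterwards the gap can be filled only by long recall.

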### Data Analysis

The primary dependent variable for this study is FAAM score at 1 week, 4 weeks, 6 months, 1 year, and 2 years. Secondary dependent variables include NPRS, modified FABQ, PANAS, LExSES, and GROC scores at 1 week, 4 weeks, 6 months, 1 year, and 2 years. The independent variable is the manual therapy intervention condition. All other outcome measures will be assessed as potential covariates of treatment success, which is defined as the achievement of minimum clinically important change score on the FAAM for this study.

Descriptive statistics will be calculated for the data set, including frequencies, means, and standard deviations. Between and within-group comparisons will be made for outcome measurements at 4 weeks, 6 months, 1 year, and 2 years post-enrolment. Analysis of variance with appropriate post-hoc pairwise comparisons will be used to assess between-groups differences for continuous data. Statistical significance of between-group differences in categorical data will be assessed with chi square analysis. Pearson correlations and multivariate linear regression analyses will be performed to determine statistical significance of associations with treatment success and failure. An intention-to-treat analysis will be performed for subjects who drop out of the study after enrolment but prior to completion of all study procedures. Statistical significance of inferential statistical tests will be accepted at α≤.05.

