### Pre-Participation Screening Measures

#### Foot and Ankle Ability Measure (FAAM)

The FAAM is a self-report questionnaire consisting of a 21-item ADL subscale and 8-item Sports subscale, in addition to a global rating of self-perceived foot function from 0-100% [41]. This inventory demonstrates satisfactory internal consistency, validity, and score stability. Test-retest validity is satisfactory for use in research designs involving repeated measures (ICC_2,1 _= .87-.89). Minimum clinically important change scores have been identified for the ADL subscale (8 points) and Sports subscale (9 points) with respect to patient global rating of change.

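### FAAM is primary at five unranked time points, each tested at .05, and 1 week is missing from the planned comparisons, so no single confirmatory test is fixed

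*Protocol article*

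**What the plan says.** All statements are in the protocol article.

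- **Primary outcome (Data Analysis):** "The primary dependent variable for this study is FAAM score at 1 week, 4 weeks, 6 months, 1 year, and 2 years".
- **Planned comparisons (same section):** "Between and within-group comparisons will be made for outcome measurements at 4 weeks, 6 months, 1 year, and 2 years post-enrolment". This list has four time points; 1 week is absent.
- **Method and threshold (same section):** "Analysis of variance with appropriate post-hoc pairwise comparisons will be used to assess between-groups differences for continuous data", and "Statistical significance of inferential statistical tests will be accepted at α≤.05". The section gives no principal time point, testing order or division of alpha.
- **Instrument (FAAM section):** "The FAAM is a self-report questionnaire consisting of a 21-item ADL subscale and 8-item Sports subscale", with a global rating from 0 to 100% as well. Each subscale has its own threshold: "Minimum clinically important change scores have been identified for the ADL subscale (8 points) and Sports subscale (9 points".
- **Sample size (Subjects, and the Figure 1 legend):** 52 per group, raised to 63 for dropout, for 80% power on an 8-point FAAM ADL difference with a 2-sample t-test at .05. No time point is named.
- **After week 4 (Treatment schedule):** "Clinicians and subjects will be free to pursue their treatments of choice after the 4-week measurements are obtained".

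**The concern.** A confirmatory trial needs one result, or a stated rule over several, that decides the question at the nominal error rate. Here five results carry equal status and each is judged at .05. The word FAAM is left open between components, and one of the five primary time points has no stated between-group comparison. That time point, 1 week, is the assessment closest to the manual technique, which is scheduled in the first two sessions, both in week 1.

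Two things are at stake. The first is the false-positive rate: if the arms do not differ, the chance that some primary comparison reaches significance exceeds 5%. The second is the freedom to choose, once results are known, which time point or subscale to present as the answer. The sample size does not settle the matter, since it covers one comparison on one subscale at an unspecified time.

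**Working it through.** **Inputs from the article:** three arms; five primary time points, four of them in the comparison list; an ANOVA at .05 each time; 52 per group for the calculation. **Assumed:** the correlation between visits, which the documents do not give, taken as equal between all pairs of visits and varied from 0 to 0.9; and two-sided tests, since sidedness is not stated.

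**1. The plan's own figures.** One FAAM score at one time point with one omnibus test has a 5% error rate, as intended. The group size of 52 does not reproduce from the d = .4 in the Figure 1 legend. With n = 2(1.96 + 0.842)²/0.4², a two-sided test needs 99 per group. At 80% power, 52 per group detects d of about .555. That mismatch is a separate matter and does not affect the error rates below; .555 is used only in step 4.

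**2. Independent visits (upper limit of the range).** The chance of at least one false positive is 1 − 0.95^k.
- k = 5: 1 − 0.7738 = 22.6%
- k = 4: 1 − 0.8145 = 18.5%

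**3. Correlated visits.** Simulation of the three-group omnibus test under no effect (normal approximation, 200,000 replicates per setting), one FAAM score. The zero-correlation column is from step 2; the simulation gave 22.7% and 18.6% there.

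| Between-visit correlation | 0 | .3 | .5 | .7 | .8 | .9 |
|---|---|---|---|---|---|---|
| Five time points | 22.6% | 21.1% | 18.7% | 15.2% | 13.1% | 10.4% |
| Four listed time points | 18.5% | 17.5% | 15.7% | 13.4% | 11.6% | 9.4% |

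Adjusting across arms does not remove the excess. A separate simulation (20,000 trials per setting, 50 per arm) with Tukey-adjusted pairs over five visits gave 21.0%, 18.7% and 15.7% at correlations .3, .5 and .7, essentially the omnibus figures.

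**4. Cost of keeping all time points primary.** Bonferroni gives .05/5 = .01 for five or .05/4 = .0125 for four. With d = .555 and 52 per group, d√(n/2) = .555 × √26 = 2.83.
- At .01: 2.83 − 2.576 = 0.254, power about 60%
- At .0125: 2.83 − 2.498 = 0.332, power about 63%

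Restoring 80% at .01 needs 2(2.576 + 0.842)²/.555² = 75.8, so 76 completers per group. The same formula gives 51 at .05. The plan recruits 63 per group, of whom 63 × 0.8 = 50.4 remain after 20% dropout.

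**The case against.** The strongest reply is that an article condenses the plan, and that a hierarchy of time points or a multiplicity rule is commonly left to the statistical analysis plan. That would answer a complaint about silence. Here the article states the five primary time points and a flat .05 for all tests, so a later document could cure this only by overriding the text. The conflict between the two time-point lists stands either way.

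It can also be said that the plan, read literally, compares groups at four time points and not five. That is fair, and the four-point figures are given for that reason; they are still about two to four times nominal. If the ANOVA were a single repeated-measures test guarding all visits, the error rate under no effect would be 5%, but the section does not say so.

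A reader might infer four stronger things, which the documents do not support:

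- **That ADL, Sports and the global rating are all primary tests.** The wording is ambiguous, but no sentence plans separate tests, and the sample size points to ADL. Only if Sports were also primary would the rate rise: to 27.8% at between-visit correlation .5 and 16.0% at .9 over five visits, with an assumed subscale correlation of .8.
- **That unadjusted pairwise testing makes the rate far higher still.** The section specifies an ANOVA with appropriate post-hoc tests. If pairs are examined only after a significant ANOVA, the rate under no effect cannot exceed the omnibus rate.
- **That free treatment after week 4 inflates false positives.** It does not. It changes what the 6-month, 1-year and 2-year contrasts estimate. Comparing initial assignments under intention-to-treat remains legitimate, and long-term outcome is a stated aim.
- **That the trial will be declared positive on any one result.** No such rule is written. The article's definition of treatment success concerns a change score on the FAAM and is not a criterion for the trial as a whole. The point is that no rule rules this out.

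**Conclusion.** The point holds. The article fixes five co-equal primary time points and a flat .05, does not name the primary subscale, and omits 1 week from the comparisons although it is primary. For one FAAM score the chance of at least one false-positive omnibus test is about 10% to 23% over five time points, or about 9% to 18% over the four listed. Those ranges rest on assumed, equal between-visit correlations from .9 down to 0 and on no true difference among the arms. Every correlation tried gives close to double the nominal 5% or more. The contradiction over 1 week and the undefined score rest on the text alone and need no assumption.

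**What to change.** 1. Name FAAM ADL at one time point as the single primary outcome. This agrees with the ADL-based, single-comparison sample size. Four weeks is a natural choice, as the last measurement before treatment becomes free; the choice is the sponsor's.
2. Control the family-wise error at .05 over the arm comparisons at that time point, for example with Dunnett or Holm for each active arm against control. State whether manipulation versus mobilization is a primary or a secondary contrast; if it is primary, include it in the adjustment.
3. Add 1 week to the list of between-group comparisons so that the two sentences agree.
4. Make the other time points, the Sports subscale and the global rating secondary.
5. Describe the 6-month, 1-year and 2-year contrasts as effects of initial assignment regardless of later treatment.

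If several time points must stay primary, state a fixed testing order or an alpha split, and restate the power; the working shows what an equal split costs.

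The preferred change alters analysis wording only, and all planned data are still collected. Its price is that the remaining time points, including the long-term ones, lose primary status. It should be settled before outcome data are seen.

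### GROC is named as a secondary outcome at five follow-ups, but the follow-up schedule lists it at none of them and the text describes it only among the baseline measures

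*Protocol article*

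**What the plan says.** Three parts of the protocol article bear on this point.

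- **Data Analysis** gives the secondary outcomes and their times: "Secondary dependent variables include NPRS, modified FABQ, PANAS, LExSES, and GROC scores at 1 week, 4 weeks, 6 months, 1 year, and 2 years".
- **Post-treatment measures and schedule** lists the instruments by time point. For the first follow-up: "The FAAM, NPRS, FABQ, PANAS, LExSES, and a side effect questionnaire will be administered at 1 week following enrolment". For the second: "The demographic questionnaire, FAAM, NPRS, FABQ, PANAS, and LExSES will be administered at 4 weeks following enrolment". The same set is then "mailed to subjects to complete at 6 months, 1 year, and 2 years following enrolment".
- **Patient Global Rating of Change (GROC)**, a subsection of Baseline Measures, describes a single-item 15-point scale "intended to measure a subject's general perception regarding response to treatment". The opening sentence of Baseline Measures says that, after screening and consent, "baseline measures will be collected on the same day".

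**The concern.** The outcome list and the measurement schedule cover the same five times but do not agree on the instruments. The GROC is to be analysed as a secondary outcome, yet neither sentence of the schedule names it. Its only place in the text is among measures taken before any study treatment, although the scale asks how the patient has responded to treatment.

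At stake is whether a named secondary outcome gets collected. Three of the five follow-ups are by mail, so an item left out of the packet is simply not asked. A rating of perceived change at a given time also cannot be properly recovered later. The GROC is the only patient-rated measure of overall change among the secondary outcomes.

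**Working it through.** No arithmetic beyond counting applies. The check sets the outcome list against the schedule, then looks for anything elsewhere that reconciles them.

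**Step 1: outcome list against schedule.** The rows are the outcomes named in Data Analysis. The entries are what Post-treatment measures and schedule provides. FABQ in the schedule is taken to be the modified FABQ of the outcome list.

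| Instrument | Role | 1 week | 4 weeks | 6 months | 1 year | 2 years | Scheduled |
|---|---|---|---|---|---|---|---|
| FAAM | primary | yes | yes | yes | yes | yes | 5 of 5 |
| NPRS | secondary | yes | yes | yes | yes | yes | 5 of 5 |
| FABQ | secondary | yes | yes | yes | yes | yes | 5 of 5 |
| PANAS | secondary | yes | yes | yes | yes | yes | 5 of 5 |
| LExSES | secondary | yes | yes | yes | yes | yes | 5 of 5 |
| GROC | secondary | no | no | no | no | no | 0 of 5 |

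Of 5 × 5 = 25 planned secondary assessments (instrument by time), 4 × 5 = 20 are scheduled. The remaining 25 − 20 = 5 are all GROC. These five gaps come from one item missing from two sentences, so they are not five separate faults.

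**Step 2: where the baseline measures fall in time.** Baseline Measures places them on the day of screening and consent. Experimental groups has randomization follow once they are recorded. Treatment schedule puts the first session within 3 days of the baseline examination. A GROC given with the other baseline measures would therefore precede both allocation and treatment, and could not express a "general perception regarding response to treatment" given in this study.

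**Step 3: other text that might resolve it.**

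- The FAAM subsection mentions a global rating of change only as the reference for the FAAM's minimum important change scores.
- The same subsection mentions a 0-100% global rating of foot function. That rates function, not change, and is not the 15-point GROC.
- Treatment schedule records an impression of improvement at 4 weeks, but it is the treating therapist's, not the patient's.
- Abbreviations only expands the acronym.

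None of these places the GROC at a follow-up, so the contradiction stands on the text.

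**The case against.** The strongest reply is that an item was dropped from a list in a condensed article. Data Analysis gives all five times for the GROC explicitly, so the intention to collect it is fairly clear. The full protocol and case report forms are not shown and may include it. Figure 2, captioned as covering the measurements after intervention, is also not shown and might list it. This stands in part: the loss of data depends on sites working from the printed schedule, and is not established. It does not remove the inconsistency. The schedule is explicit enough to name a side effect questionnaire at one visit and a demographic questionnaire at the others, so two explicit lists disagree. If Figure 2 does show the GROC, it would conflict with the written schedule.

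A second reply is that the subsections under Baseline Measures serve to describe instruments. NPRS, FABQ, LExSES and PANAS are also described only there, and all are follow-up outcomes. That is fair: GROC administration at baseline is inferred from the heading and its opening sentence, and no planned analysis names a baseline GROC value. But no exception is stated for the GROC, and a literal reader could give it then.

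A reader might also infer that, because the FAAM's minimum important change was identified against a global rating of change, missing GROC data would cost the trial a check on its own success threshold. The documents do not support this. They report the change scores as already established, define success by the FAAM score alone, and plan no re-check against the GROC.

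**Conclusion.** The point holds as an internal inconsistency between the outcome list and the follow-up schedule, with an unclear placement under Baseline Measures. Confidence is high for the inconsistency. It is only conditional for the consequence: if the schedule is followed as written, one of five secondary instruments would have no data at any of its five follow-ups.

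The effect is contained. The primary FAAM outcome, the sample size and the definition of treatment success do not depend on the GROC. The correction should be made, but the main comparison is not threatened.

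The conclusion assumes that the article's two written lists are each meant to be complete for the times they name, and that nothing in Figure 2 or in documents not shown overrides them. Even if something does, the published text would still need correcting.

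**What to change.** Reconcile the three places in the text:

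1. In Post-treatment measures and schedule, add the GROC to the 1-week form, the 4-week form and the packets mailed at 6 months, 1 year and 2 years.
2. In Baseline Measures, or in the GROC subsection, state that the GROC is not collected at baseline.
3. Compare it between arms at the times Data Analysis already sets for comparisons: 4 weeks, 6 months, 1 year and 2 years. That section names the GROC as an outcome at 1 week too but lists no comparison then, so a 1-week comparison would be an addition and should be declared as one.

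If the sponsor does not intend to collect the GROC, the alternative is to remove it from the secondary outcomes in Data Analysis. Figure 2 and the forms should be checked to agree with whichever route is taken.

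The cost of the first route is one single-item question on forms and mailings that already exist, plus one clarifying sentence. The sample size and the primary analysis do not change.
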